## Results

The LuAna trial received institutional ethics board approval and was formally activated in October 2024. Data collection began in January 2026 with a projected end date of September 2026. At interim review (November 2025), 3 of the 13 participating centers had completed all site activation requirements and were prepared to initiate enrollment. The trial is currently ongoing with active data collection. Data analysis is scheduled for completion by November 2026, and results dissemination is expected by January 2027.

## Discussion

### Principal Findings

This trial is a pivotal effort to evaluate how AI can enhance diagnostic accuracy, clinical workflows, and physician performance in interpreting chest radiographs.

By using a batched stepped-wedge cluster-randomized design across a nationally representative sample of health care settings, we aim to rigorously assess the real-world utility of LuAna, an AI-powered platform for CXR interpretation developed in the public sector to assist general practitioners.

Despite ongoing debate about the advantages of SW-CRTs, including concerns about equipoise and delayed access to interventions [41], this design offers distinct benefits for implementation research. Governed by the same ethical principles as all clinical research [42], SW-CRTs are particularly valuable when evaluating innovations that are expected to be beneficial and for which withholding access may be contentious [42]. In the SUS context, this approach ensures that all centers ultimately gain access to AI support, promotes fairness and acceptability, and provides a pragmatic pathway to sustainable integration of the intervention into routine care.

The central goal is to determine whether LuAna improves clinicians’ ability to detect radiographic abnormalities, particularly in environments with limited access to radiology expertise. Comparisons against adjudicated, double-blinded radiologist interpretations will enable the quantification of diagnostic agreement, while stratified analyses by site type and physician characteristics will offer insights into contextual factors that may influence AI performance.

Importantly, the trial also investigates the clinical impact beyond diagnostic accuracy. By evaluating patient management decisions and turnaround times, we aim to capture how AI affects treatment pathways and efficiency in routine care. Usability assessments will provide critical feedback for refining and scaling the platform, thereby ensuring seamless integration into diverse clinical workflows across both mobile and desktop interfaces.

Robustness will be evaluated through sensitivity analyses on image quality, artifacts, and medical devices, thereby validating the model’s generalizability under real-world conditions. Additionally, longitudinal analysis of physician interpretations will explore whether repeated AI exposure improves independent performance, highlighting AI’s potential educational role.

Beyond its methodological rigor, the LuAna trial advances an area in which robust evidence remains scarce: the real-world, prospective clinical evaluation of AI tools. While algorithmic performance is well documented in retrospective studies, few investigations have examined how AI behaves once deployed within the operational complexity of large, heterogeneous public health systems [40,43,44]. This gap has been repeatedly highlighted by international frameworks, including the DECIDE-AI (Developmental and Exploratory Clinical Investigation of Decision Support Systems Driven-Artificial Intelligence) guidelines, which emphasize the need for pragmatic, early-stage clinical evaluation before widescale deployment. Indeed, studies show positive primary outcomes for AI in clinical practice, but concerns remain due to mostly single-center trials, limited demographic data, and inconsistent reports on operational efficiency, which affect generalizability and practical use [45,46].

Evaluating AI-based decision-support systems involves several challenges: understanding their nature as complex interventions; considering user variability and the biases it introduces; integrating human factors into the collaboration between clinicians and AI; assessing both real patients and their data; dealing with continuous system changes; preventing the reproduction of health inequalities; ensuring that results generalize to different contexts; and guaranteeing reproducibility in the real world. By implementing LuAna across a nationally diverse range of health care settings, this study not only provides valuable empirical data on AI performance in real-world situations but also offers a unique opportunity to examine issues related to fairness [47-49].

Variability in patient demographics, imaging equipment, staffing, and workflow conditions across Brazil’s public health system creates a natural stress test for equity: the trial can assess whether AI-assisted interpretation benefits all subpopulations and settings equally or whether performance disparities emerge [50,51]. In doing so, it addresses 2 critical gaps in the global AI literature—real-world clinical validation and algorithmic fairness—offering evidence that is seldom available yet essential for responsible, scalable, and equitable integration of AI into routine care.

Grounded in operational realities and health care equity, this study contributes to a broader movement toward responsible, evidence-based AI integration in clinical practice. It aligns with international recommendations for validation frameworks and addresses a global need for tools that are both technically robust and contextually appropriate for low- and middle-income health systems.

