### Statistical Analysis

The sample size was calculated to detect a minimum difference of 10% in the primary outcome—a binary indicator of whether the physician correctly labeled a CXR—between the AI-assisted and control groups. The calculation accounted for the stepped-wedge cluster-randomized design with batched implementation using the following assumptions: 9 clusters randomized in 3 batches to cross over from control to intervention, 10 time periods, a baseline detection rate of 67% in the control group, an expected increase to 77% in the intervention group, and an intracluster correlation coefficient ranging from 0.001 to 0.003.

The design effect was adjusted for the correlation structure induced by repeated measures within clusters over time using methods described by Hussey and Hughes [28] and extended to account for batched randomization, as described by Hemming et al [35,36]. The power calculation targeted 80% power at a 2-sided significance level of 5% and accounted for potential variability in cluster sizes. The final average cluster size was 37, and the overall sample size was inflated by 10% to account for anticipated exclusions due to image quality issues or missing data (dropout). This approach ensures adequate power to detect a meaningful effect of the intervention while maintaining the integrity of the stepped-wedge design with staggered implementation across batches.

Primary analysis will follow the modified intention-to-treat principle. All eligible CXRs (the unit of analysis in this study) will be analyzed according to the study group (control or intervention), to which their corresponding cluster was allocated at the time of image acquisition, regardless of physician adherence to the intervention or exposure to AI output. Images of poor quality, as defined by our radiologists, will be excluded postrandomization.

The primary outcome analysis will use a generalized linear mixed model with a binomial distribution and logit link function to estimate the effect of the AI-assisted intervention on detection probability. The model will include fixed effects for the intervention group (AI-assisted vs control), calendar time (to adjust for secular trends), time since intervention rollout (to account for learning or adaptation effects), and batch effects. In addition, random intercepts for clusters will be specified to account for intracluster correlation.

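### Stratified analyses, the only method named for differences by site type and physician characteristics, do not estimate or test whether the AI effect differs; an interaction term with a confidence interval does

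*Protocol article*

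**What the plan says.** Two statements under Principal Findings in the Discussion bear on effect differences. One names the method: "stratified analyses by site type and physician characteristics will offer insights into contextual factors that may influence AI performance". The other names the question: "the trial can assess whether AI-assisted interpretation benefits all subpopulations and settings equally or whether performance disparities emerge".

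The Statistical Analysis section describes the primary mixed model. Its fixed effects are intervention group, calendar time, time since rollout and batch, with a random intercept for cluster. It lists no product of intervention with site type or with any physician characteristic. Physician characteristics otherwise appear in that section only in relation to the questionnaire answers on the mobile interface. How strata would be compared is not stated.

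**The concern.** Whether AI helps one setting more than another is a question about a difference between two effects. Separate stratum estimates, each with its own P value, do not answer it. Each stratum rests on only part of the films, so strata that share the same true effect will often fall on opposite sides of the significance threshold by chance.

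For a tool meant for national use, two wrong conclusions are possible. One is that AI helps only in some kinds of site. The other is that it helps all equally because no stratum stood out.

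**Working it through.** **Inputs from the article.**
- Rates: "a baseline detection rate of 67% in the control group, an expected increase to 77% in the intervention group".
- Layout: "9 clusters randomized in 3 batches to cross over from control to intervention, 10 time periods". The design figure is not shown, so several layouts were tried.
- Correlation: "an intracluster correlation coefficient ranging from 0.001 to 0.003".
- Size: "The final average cluster size was 37". The text does not say whether this is per cluster or per cluster-month.
- Centres: "3 of the 13 participating centers had completed all site activation requirements".

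**Assumptions.** 37 films per city-month, a true 10-point effect in every stratum, one type per centre, and the stratum shares given below. The calculations use a normal approximation on the proportion scale with a random city intercept and leave out the time-since-rollout term.

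**1. The plan's own figure.** With a Hussey-Hughes variance and 37 per city-month, overall power depends on the layout:
- 73–76% for three batches with batch-specific periods (four periods each, or run to the end)
- 85–93% for batches run to the end with shared periods
- 94–97% for eight-period batches
- 98.5–99.7% for an unbatched wedge

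With 37 per city in total, power is 15–35%. The figure of 37 can therefore be neither confirmed nor refuted. The point does not depend on it.

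**2. Check by hand, taking overall power as 80%.** The overall effect then lies 1.960 + 0.842 = 2.802 standard errors from zero. If precision is proportional to a stratum's share f, its power is Φ(2.802√f − 1.960).
- 50:50: 2.802 × 0.707 = 1.981, power Φ(0.021) = 0.508. Exactly one of the two significant: 2 × 0.508 × 0.492 = 0.50.
- 80:20: powers Φ(2.506 − 1.960) = 0.707 and Φ(1.253 − 1.960) = 0.240. Exactly one significant: 0.707 × 0.760 + 0.293 × 0.240 = 0.61.
- Three equal strata: 2.802 × 0.577 = 1.618, power Φ(−0.342) = 0.366. Some but not all significant: 1 − 0.366³ − 0.634³ = 0.70.

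**3. With the trial's own structure.** If each centre has one type, 13 centres in 9 cities leave 13 − 9 = 4 second centres, so at most 4 cities can be mixed. With two site types and 4 mixed cities, generalised least squares over several layouts gives disagreement in significance in about 19–48% of trials.

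Three equal strata within every city give about 49–75%. For site type that would need 3 × 9 = 27 centres, so this range is only an illustration. One worked case is one city crossing per month, with batch terms and ICC 0.001:
- The SE of the difference between two separately fitted strata is 6.44 points, so each stratum has SE 6.44/√2 = 4.55.
- Power is Φ(10/4.55 − 1.960) = 0.59.
- Disagreement is 1 − 0.593³ − 0.407³ = 0.72.

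Under the same common effect, an interaction test is significant 5% of the time by construction.

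**4. Does one model also gain precision?** In the same case:

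| Fit | SE of the difference (points) | Information relative to separate fits |
|---|---|---|
| Separate strata | 6.44 | 1 |
| One model, stratum-specific month and batch effects | 6.42 | (6.44/6.42)² = 1.01 |
| One model, shared month and batch effects | 3.81 | (6.44/3.81)² = 2.86 |

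Across layouts the shared-trend model carries about 1.4 to 3.4 times the information. If trends may differ, the gain is a few percent, at most about 19%.

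**5. Power of the interaction itself.** For a 50:50 split with stratum-specific trends, the SE of the difference is twice the overall SE. A 10-point difference between strata then has power Φ(2.802/2 − 1.960) = Φ(−0.559) = 0.29. With shared trends it is about 45–55%.

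**The case against.** The naming clause is one sentence in the Discussion, worded as exploratory. No section says that significance will be compared across strata or that interaction terms are ruled out. Subgroup estimates are often shown beside an interaction test, and an article may leave that detail to the analysis plan. This stands. A reader might infer that the trial has decided to judge differences by separate P values, and the text does not support that.

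A reader might also infer that stratifying throws away half or more of the information. That is not supported as a general statement. The strata together use every film, and step 4 shows that nearly all the gain comes from assuming one calendar trend for all subgroups. Whether to assume that is a trade of bias against variance.

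The clause also speaks of AI performance, which might mean the algorithm's accuracy by site, where reporting by stratum is normal. That reading is possible for part of it. But the same paragraph opens with clinicians' ability to detect abnormalities, and the equity statement concerns AI-assisted interpretation.

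Finally, the Limitations section already concedes that equity analyses are limited, and an interaction test would have modest power. Both are true, and both keep the results exploratory. Neither makes separate strata an answer to the question posed.

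**Conclusion.** The point holds in limited form. The article names one method for differences by setting and reader, and pairs it with a question about equal benefit that this method cannot answer. If strata were read separately, a common 10-point effect would appear in only one of two site types in about 19–48% of trials, against a nominal 5% for a direct test. That range rests on 37 films per city-month, the stated ICC range, 4 mixed cities and layouts that the text does not fix.

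The risk of a false claim does not depend on a common calendar trend; a large gain in precision does. The primary analysis is unaffected.

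**What to change.** State that differences by site type and physician characteristics will be estimated as intervention-by-site-type and intervention-by-physician-characteristic terms in the primary mixed model fitted to all films, each with a 95% CI. Show stratum estimates as description only. Say that a non-significant difference will not be read as equal benefit, and that these results are exploratory. Add a sensitivity model in which the calendar trend may differ by subgroup.

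The cost is wording and a few model terms, with no new data. The Results section schedules completion of the analysis for November 2026, so the change can be made beforehand. The downside is that the main interaction model assumes a common calendar trend. If the sensitivity model is preferred, most of the precision gain over separate fits is lost, but the direct test of the difference remains.

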### Limitations

Although the stepped-wedge design enhances real-world applicability by including diverse health care settings, the findings may still be influenced by context-specific factors, such as infrastructure, physician training, and patient demographics. Variation in image acquisition, whether from printed films, computer displays, or mobile capture, may introduce heterogeneity that affects both physician interpretation and algorithm performance. In addition, while the trial evaluates diagnostic accuracy, turnaround times, usability, and model robustness, it does not directly measure patient-level outcomes such as morbidity or mortality. Equity analyses are further limited by the narrow range of demographic variables collected, which may not fully capture socioeconomic or clinical determinants of performance. Finally, the lack of detailed clinical data, including comorbidities, treatment history, and laboratory findings, restricts the ability to contextualize radiographic interpretations and fully assess the AI integration into patient care pathways.

### Conclusion

Future work should prioritize expanding datasets to include a broader spectrum of acquisition standards, additional radiographic projections (eg, lateral views), and complementary imaging modalities such as CT. Scaling to additional centers across Brazil—capturing greater geographic, demographic, and service-level diversity—will further strengthen dataset representativeness and enhance algorithm robustness. The adoption of standardized annotation protocols will support higher-quality data curation and reduce uncertainty in the reference standard. In parallel, strategies such as transfer learning and active learning should be explored to optimize performance in data-limited environments.

Ultimately, LuAna seeks to demonstrate that AI-powered diagnostic support can be safely and effectively integrated into public health care, empowering clinicians and improving outcomes for underserved populations. This study will lay the groundwork for broader AI adoption in medical imaging, grounded in evidence, equity, and clinical impact.

If proven effective, LuAna could help bridge diagnostic gaps by supporting nonspecialist clinicians, accelerating decision-making, and strengthening health care delivery in underserved regions, offering a scalable, evidence-based model for equitable AI integration in medical imaging.
